### Data handling and safety monitoring

All data will be collected in compliance with the approved protocol and will be recorded on a CRF. All adverse events that are not necessarily related to the treatment will be observed and reported by the participants and researchers at each visit. In the event of serious adverse reactions, detailed reports will be drafted and assessments will be made based on the protocol. Blood tests, including complete blood count, differential count, and renal and liver function tests, will also be performed at the screening visit and after the end of treatment. Data and safety monitoring will be conducted at all sites periodically during the study.

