**Methods/design:**

In this multicentre, assessor-blind, three-arm, parallel-design, randomised controlled trial, 150 participants will be assigned to the EA group, the sham EA (SEA) group, or the usual care group. The EA and SEA groups will receive the specific treatments 2–3 times a week for 4 weeks, for a total of 10 sessions, whereas the usual care group will not receive EA and will continue with usual care during the same time period. The primary outcome measure will be changes in the Insomnia Severity Index 5 weeks after randomisation. The secondary outcomes will include the Pittsburgh Sleep Quality Index, the Hospital Anxiety and Depression Scale, a sleep diary, the EuroQoL-5 dimension questionnaire, the levels of melatonin and cortisol, and the Patient Global Impression of Change. Safety will be assessed at each visit.

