## Methods/design

### Study design and setting

We designed a multicentre, randomised, assessor-blind, controlled, parallel-group study to compare the effect and safety of EA, sham electroacupuncture (SEA), and usual care in subjects with insomnia. The participants will be recruited using regional newspapers, flyers, advertisement boards, etc. Potential candidates for the study will be screened and fully informed about the study. Eligible participants will be randomly assigned to three groups and receive treatment for 4 weeks with 2 months of follow-up. The study flow chart is shown in Fig. 1. The Standard Protocol Items: Recommendations for Interventional Trials (SPIRIT) checklist and figure are given in Additional file 1 and Fig. 2, respectively.

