To observe physiological changes in the patient, the levels of salivary melatonin and cortisol will be assessed. Melatonin is secreted from the pineal gland and has a direct effect on sleep structure [23]. Cortisol is produced in the adrenal cortex and its secretion is regulated by the hypothalamic-pituitary-adrenal axis. Studies have shown that changes in cortisol concentrations are associated with stress and sleep [24]. Because both melatonin and cortisol concentrations can fluctuate according to a circadian rhythm, the samples will be collected and analysed after scheduling the participant visit and conducting educational sessions on the use of the saliva collection kit in advance [25].

The EuroQoL five dimension questionnaire (EQ-5D) will be used to measure health-related quality of life. This instrument is designed to have the subject check the most appropriate response to five items on health status; each checked item will have a weighted score of 1, 2, or 3, and the combination of the five numbers will represent the health status of the subject [26]. In addition, the EQ-5D and ISI will be used to estimate the parameters needed for economic evaluation. The Patient Global Impression of Change (PGIC) will be used to assess the participant’s subjective perception of overall improvement after treatment.

The time points for each assessment and the procedures are summarized in Table 2.

**Table 2 Tab2:** Schedule for treatment and outcome assessment

Visit	Screening	1	2–5	6	7–10	11	12	13
Week		1	1–2	3	3–4	5	9	13
Informed consent	●							
Inclusion/exclusion criteria	●							
Treatment expectation questionnaire	●							
Vital signs	●	●	○	●	○	●	●	●
Demographic characteristics	●							
Medical history	●							
Laboratory tests	●					●		
Random allocation		●						
Change of medical history		●	○	●	○	●	●	●
EA treatment		○	○	○	○			
ISI	●	●		●		●	●	●
Melatonin/cortisol study		●				●		
PSQI		●		●		●	●	●
Sleep diary	●	●		●		●	●	●
HADS	●	●		●		●	●	●
EQ-5D		●		●		●	●	●
PGIC				●		●	●	●
Blinding test		○			○			
Safety assessment		●	○	●	○	●	●	●

●, All groups; ○, treatment groups

*EA* electroacupuncture, *EQ-5D* EuroQoL five dimension questionnaire, *HADS* Hospital Anxiety and Depression Scale, *ISI* Insomnia Severity Index, *PGIC* Patient Global Impression of Change, *PSQI* Pittsburgh Sleep Quality Index

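### Usual care has 4 post-baseline safety enquiries against 12 in EA and SEA, so an unadjusted safety comparison with usual care may overstate minor, transient events in the treated arms

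*Protocol article*

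**What the plan says.** Study design and setting gives the purpose as to "compare the effect and safety of EA, sham electroacupuncture (SEA), and usual care in subjects with insomnia", so usual care is part of the safety comparison.

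Collection of events is tied to visits. The abstract states "Safety will be assessed at each visit", and Data handling and safety monitoring says that adverse events, whether or not related to treatment, "will be observed and reported by the participants and researchers at each visit". The article describes no collection between visits.

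The number of visits depends on the arm. EA and SEA are treated "2–3 times a week for 4 weeks, for a total of 10 sessions". Participants in usual care attend no such sessions. Table 2 follows this. Its footnote separates filled from open circles ("All groups; ○, treatment groups"). In the row "Safety assessment", visits 1, 6, 11, 12 and 13 are filled and apply to everyone. Visits 2–5 and 7–10 are open and apply to EA and SEA only. Laboratory tests, by contrast, are scheduled equally, at screening and visit 11.

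**The concern.** How many minor events are recorded depends partly on how soon after the event a person is asked. In weeks 1–4, EA and SEA participants are asked every few days, while usual-care participants are asked about once a fortnight. A brief headache or a day of dizziness is more likely to reach the case report form in the treated arms even if it is equally common in all three. Because events count whatever their cause, such background complaints are included.

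Usual care is the only arm that shows the event rate without needling or sham. If its rate is under-recorded relative to the other two, the comparison with it may make EA look less safe than it is. Safety is part of the stated objective. The primary endpoint is not touched.

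**Working it through.** The article gives no calculated figure for safety, so the starting point is a count from Table 2.

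**Scheduled safety enquiries**

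| Period | EA and SEA | Usual care |
|---|---|---|
| Visit 1 (randomisation) | 1 | 1 |
| Visits 2–5 | 4 | 0 |
| Visit 6 (week 3) | 1 | 1 |
| Visits 7–10 | 4 | 0 |
| Visit 11 (week 5) | 1 | 1 |
| Visits 12 and 13 (weeks 9 and 13) | 2 | 2 |
| Total | 13 | 5 |
| Total after visit 1 | 12 | 4 |

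Visit 1 is the randomisation visit, with no post-randomisation period before it, so 12 versus 4 is the relevant count. From visit 1 to week 5 it is 10 versus 2; in follow-up it is 2 versus 2. The whole excess, 12 − 4 = 8, lies in weeks 1–4.

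**From enquiries to recorded events (illustration)**

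The article gives neither event rates nor a recall period, so what follows rests on assumptions:
- True event rates are constant and equal in all arms.
- An event that happened t days before the next enquiry is reported with probability exp(−λt), where λ = ln 2 / h and h is the recall half-life.
- Week 1 to week 5 is 28 days. The mean gap is 28/10 = 2.8 days in EA and SEA and 28/2 = 14 days in usual care. The two later gaps are 28 days in every arm.

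For events spread evenly over a gap of g days, the share captured is

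f(g) = (1 − exp(−λg)) / (λg).

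For h = 7, λ = 0.0990, so f(2.8) = 0.242/0.277 = 0.873, f(14) = 0.750/1.386 = 0.541 and f(28) = 0.9375/2.773 = 0.338.

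| Half-life h | f(2.8) | f(14) | f(28) | Ratio, weeks 1–4: f(2.8)/f(14) |
|---|---|---|---|---|
| 7 days | 0.873 | 0.541 | 0.338 | 1.61 |
| 14 days | 0.934 | 0.721 | 0.541 | 1.29 |
| 28 days | 0.966 | 0.845 | 0.721 | 1.14 |
| Full recall | 1 | 1 | 1 | 1.00 |

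Over the whole schedule, 28 days of unequal gaps are followed by 56 days of equal ones:

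ratio = [28·f(2.8) + 56·f(28)] / [28·f(14) + 56·f(28)].

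- h = 7: (24.4 + 18.9)/(15.1 + 18.9) = 1.27
- h = 14: (26.2 + 30.3)/(20.2 + 30.3) = 1.12
- h = 28: (27.0 + 40.4)/(23.7 + 40.4) = 1.05

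EA and SEA share the same schedule, so their ratio is 1.0 throughout.

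**The case against.** The best case for the plan is that the asymmetry comes with the design. Usual care has no sessions to attend, asking about harms at each session is ordinary practice, and SEA has the same visits as EA, so the comparison that bears on attribution is sound. Laboratory tests are balanced. Change of medical history is recorded in all arms at the common visits, and all participants are asked to report new treatments, which helps to capture events that needed care. Recall windows and safety tables are usually set out in a full protocol or analysis plan. All of this stands, and it confines the point to minor, transient events compared with usual care. It does not remove it: the unequal schedule is stated, the three-arm safety aim is stated, and nothing in the article reconciles them.

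Three stronger readings are tempting but unsupported.

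- A reader might take 13 versus 5 (2.6-fold), or 12 versus 4 (3-fold), as the size of the bias. These ratios count questions. Giving each enquiry a fixed 5% yield would produce 1 − 0.95^13 = 49% versus 1 − 0.95^5 = 23% of participants with an event, but this lets a question covering about 3 days yield as much as one covering 14 or 28. That makes events scale with the number of questions instead of time at risk.
- A reader might infer that a chi-square or Fisher test of adverse events against usual care is planned. Statistical analysis assigns those tests to categorical data in general, and adverse events are not among the outcomes listed there. A descriptive table would carry the same imbalance.
- A reader might conclude that EA is bound to look less safe. With full recall there is no distortion, so the supportable word is may.

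The obvious remedy also has a trap. Dropping events that EA participants reported at sessions would remove events arising around needling and could tilt the comparison towards EA.

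**Conclusion.** The point holds in limited form. The schedule gives EA and SEA 12 post-baseline safety enquiries and usual care 4, with the whole difference in weeks 1–4. An unadjusted comparison of event counts or incidence with usual care may therefore overstate minor, transient events in the treated arms. EA versus SEA is unaffected; serious events and laboratory findings should be largely so.

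The direction is likely, but the size is not known from the article. Across assumed half-lives of 7 to 28 days the spurious ratio runs from about 1.6 down to 1.1 in weeks 1–4 and from about 1.27 down to 1.05 over the whole schedule. It rests on equal and constant true rates, the assumed recall decay and the average visit gaps.

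**What to change.** 1. Name EA versus SEA, using all visits, as the main comparative safety analysis.
2. For EA versus usual care, put the same question, covering the time since the last common visit, to all arms at visits 6, 11, 12 and 13. Count every event reported in answer, including EA events already reported at a session.
3. Report all session-elicited events in full in a separate table, without a test against usual care.
4. State the unequal ascertainment when the results are reported.

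The cost is one repeated question, a flag on the case report form for the visit at which an event was elicited, and one more table. Treatment and sample size do not change. Trial status says that recruitment is under way, so the question and flag can be introduced for remaining participants. For those already seen, a common-visit analysis depends on whether the visit of report was recorded; failing that, step 4 is the minimum.

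Two limits remain. EA and SEA participants will have been prompted at sessions, so recall at the common visits may still not be fully equal. The usual-care comparison may also miss some short-lived EA events, so it must not be read as the full EA event rate.

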## Discussion

This study is a multicentre randomised controlled clinical trial with an appropriate sample size on the effect and safety of EA for treating patients with insomnia disorder according to the criteria of the DSM-5.

The differentiation of primary and secondary insomnia which existed in the previous sleep disorder diagnosis systems was excluded in the DSM-5 diagnostic system [27]. There is currently no conclusive causal relationship or direction between sleeplessness and other co-existing medical or psychiatric illnesses [27]. Insomnia does not simply mean experiencing difficulty sleeping during the night, and it has a considerable negative impact on various aspects including daytime functioning, emotion, quality of life, and socio-economic burden. Therefore, it is important to make a comprehensive assessment of all these domains in clinical trials that evaluate the therapeutic effect on insomnia [28].

In the present study, ISI and PSQI will be used to assess the insomnia symptom severity, the chief complaints of insomnia patients. The ISI was selected as the primary outcome to assess the effects of EA on insomnia because it can directly assess the severity of insomnia, disruption to quality of life, and interference with daytime activities over the past 2 weeks. A sleep diary will be evaluated as a sleep/wake parameter in addition to the questionnaires. The HADS will be used to assess the psychological symptoms such as anxiety and depression, which are commonly associated with insomnia patients. The PGIC will be used as a global assessment outcome measurement. Quality of life will be evaluated using the EQ-5D. Moreover, there are several reports indicating patients with sleep disorders use more health care resources [29, 30]. As a result, an additional economic evaluation will be conducted to investigate the cost-effectiveness of electroacupuncture treatment for insomnia disorder.

EA has been used in various clinical conditions, including insomnia and psychiatric disorders. However, the mechanisms underlying the effect of EA have not yet been elucidated. A study by Tang et al. reported that low-frequency EA is an effective treatment for post-stroke insomnia and can regulate the level of neurotransmitters, including 5-hydroxytryptamine and norepinephrine in patients with post-stroke insomnia [31]. Additionally, insomnia has been shown to be related to changes in melatonin and cortisol levels, and several previous studies reported the efficacy and safety of using melatonin to treat insomnia [32–34]. Melatonin is a hormone secreted from the pineal gland in the brain and is important for regulating the sleep/wake circadian rhythm. In general, melatonin is secreted at high levels immediately before sleep and during the night, but its serum concentration decreases during the daytime and activity. Nordio et al. assessed the 24-h urinary melatonin metabolite rhythm and suggested that acupressure at the H7 acupoint may involve regulation of melatonin [35]. Spence et al. also reported that acupuncture increased the nocturnal endogenous secretion of melatonin and improved polysomnographic measures [36]. Cortisol is closely associated with the stress response and can cause insomnia when produced in excessive amounts [24]. Previous studies using animal models have reported that GV20, EX-HN3, and HT7 needling or EA stimulation can suppress the secretion of cortisol [37, 38]. In the present study, the levels of melatonin and cortisol will be analysed before and after treatment to explore the physiological mechanism of EA in the treatment of insomnia.

There are limitations to this study. First, we will perform sham electroacupuncture using a sham EA device and PSD as a control intervention in the SEA group. However, the currently developed sham acupuncture interventions are not completely inert physiologically, and previous studies reported that sham acupuncture interventions not only have some physiological activity, but could also be associated with larger effects than pharmacological and other physical placebos [39–41]. Placebo effects are very commonly observed and should be controlled appropriately in sleep disorder clinical trials [42]. Therefore, we will apply the non-penetrating placebo device at non-acupoints to minimize this bias, and we will also include a usual care group as a control. Second, although PSG is generally considered the gold standard in sleep studies, it is not always included in actual clinical trials due to its costs, burden on patients, and research conditions. In the present multicentre trial, PSG is not feasible and various outcome measures including a sleep diary, ISI, PSQI, HADS, melatonin and cortisol will be assessed. We will evaluate objective sleep parameters such as PSG or actigraphy in future studies. In spite of its limitations, the results of this multicentre randomised controlled trial may provide rigorous evidence for a multi-faceted evaluation of the effect and safety of EA for treating insomnia.

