#### Exclusion criteria

Individuals meeting any of the following criteria will be excluded:a diagnosis of major depressive disorder, anxiety disorder, panic disorder, or other psychiatric disorders; caffeine, alcohol, or drug addiction; or a Hospital Anxiety and Depression Scale (HADS) score ≥11 points;working shifts or changes in day/night work schedule that could impact circadian rhythm;suffering from pain severe enough to cause sleep disturbance or presence of any disease that could cause insomnia;having undergone any therapy or taken any medication as required in the previous 2 weeks, or a change in the type or dosage of a regularly taken medication in the previous 4 weeks to alleviate insomnia;taking medication for a cardiovascular or haemostatic disorder;a diagnosed unregulated hormone disorder, serious or systemic disease (e.g. hyperthyroidism, chronic liver disease or chronic kidney disease) that could affect sleep;a previous hypersensitivity reaction to acupuncture or difficulty co-operating with acupuncture therapy;the presence of implants that could interfere with EA or a history of hypersensitivity to electrostimulation;pregnancy, lactation, or planning a pregnancy; anddifficulty complying with the treatment, questionnaire, or study protocol

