### Interventions

The EA group will be treated with 0.25 × 40 mm disposable sterilized filiform needles (Dong-bang Acupuncture Inc., Seoul, Korea) applied to the Baihui (GV20), Yintang (EX-HN3), bilateral Shenmen (HT7), Neiguan (PC6), Jinmen (BL63), and Dazhong (KI4) acupoints by inserting and manipulating the needle to achieve *de qi* (2–3 times a week for 4 weeks, for a total of 10 sessions). After *de qi* is achieved, an EA device (ES-160, Ito Co. Ltd., Tokyo, Japan) will be used to apply 4 Hz for 30 min at 80% intensity of the stimulation felt by the participant.

For the SEA group, a Park Sham Device (PSD; Dong-Bang AcuPrime Ltd., Exeter, UK) will be used to needle 10 specific non-acupoints on both the arms and legs during the same period using the same needling schedule as the EA group. The PSD is one of many sham acupuncture methods used in acupuncture studies [14, 15]. It has a blunt end that retracts to shorten the length of the needle and give the appearance that needling will be performed without the needle actually penetrating the skin. Electrostimulation in the SEA group will be performed using the same EA device (ES-160) that is used in the EA group. The de-activated device will be connected to the PSD and applied for 30 min, while making the same beeping sound and light indicators when operated without delivering any electrostimulation.

The EA and SEA groups will be prohibited from undergoing any additional treatments for insomnia during the study period. The planned acupuncture treatment is based on Standards for Reporting Interventions in Clinical Trials of Acupuncture (STRICTA) and Consolidated Standards of Reporting Trials (CONSORT), and detailed information is summarized in Table 1.

**Table 1 Tab1:** Details of acupuncture treatment based on the revised STRICTA checklist

	Item	Detail
1. Acupuncture Rationale	1a) Style of acupuncture	EA based on traditional medicine theory
	1b) Reasoning for treatment provided, based on historical context, literature sources, and/or consensus methods, with references where appropriate	Textbook on acupuncture and Moxibustion, related literature [10–12, 43], consensus by experts in acupuncture and insomnia
	1c) Extent to which treatment was varied	Standardized treatment
2. Details of acupuncture	2a) Number of needle insertions per subject per session	Fixed 10 acupoints
	2b) Names of points used	EA treatment group: Unilateral GV20, EX-HN3, bilateral HT7, PC6, BL63, KI4

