	2c) Depth of insertion	From 5 to 20 mm
	2d) Response sought	*de qi* during needling and perception of stimulus during electrostimulation
	2e) Needle stimulation	After manual stimulation, 4 Hz will be conducted and stimulation will be at 80% intensity of the stimulus the participant perceives
	2f) Needle retention time	30 min
	2 g) Needle type	0.25 × 40 mm sterilized stainless steel needle
3. Treatment regimen	3a) Number of treatment sessions	Total 10 sessions
	3b) Frequency and duration of treatment sessions	2–3 sessions per week for 4 weeks
4. Other components of treatment	4a) Details of other interventions administered to the acupuncture group	All three groups will be educated through sleep hygiene brochure. Usual care group will be permitted to have any type of treatment
	4b) Setting and context of treatment, including instructions to practitioners, and information and explanations to patients	The practitioner will limit unnecessary conversation that does not pertain to the treatment or patient
5. Practitioner background	Description of participating acupuncturists	Korean Medical Doctors who have a license and at least 2 years of clinical experience
6. Control or comparator intervention	6a) Rationale for the control or comparator in the context of the research question, with sources that justify this choice	Park sham placebo device will be used as a sham control [12, 14]
	6b) Precise description of the control or comparator. If sham acupuncture or any other type of acupuncture-like control is used, provide details as for items 1–3 above.	SEA control group: use Park sham placebo device on 10 non-acupoints on both upper and lower limb and connect the electrostimulator in switch-off state for removal after 30 min

*EA* electroacupuncture, *STRICTA* Standards for Reporting Interventions in Clinical Trials of Acupuncture

The usual care group will be allowed to undergo any treatment for insomnia except traditional medicine such as acupuncture, moxibustion, and herbal treatment. The participants will be asked to inform the research investigators of any new treatments received after entry into the trial, and all concomitant treatments will be recorded on the case report form (CRF). All three study groups will be educated using a brochure on sleep hygiene.

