### Statistical analysis

The primary outcome measure in this study is the mean change in the ISI from baseline to week 5. A two-sided test with a significance level of 0.025 will be performed using an analysis of covariance with baseline as the covariate and the treatment group as the fixed factors. The intra-group ISI changes from baseline to post-treatment will be analysed using Student’s paired *t* test or Wilcoxon signed-rank test, and reported with a 95% confidence interval. In addition, we will use a repeated-measures analysis of variance to identify any trend changes. Dunnett’s test will be used for inter-group comparisons to compensate for multiple comparisons.

The methods used to analyse the secondary outcome measures, i.e. ISI at weeks 3, 9, and 13, PSQI, HADS, EQ-5D, PGIC, changes in sleep diary entries, and changes in melatonin and cortisol levels, will be the same as those used for the primary assessment analyses. The chi-square test or Fisher’s exact test will be used for categorical data. Analyses will be conducted on an intent-to-treat basis, and multiple imputations will be applied if there are missing values.

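### Salivary melatonin is meant to show how EA works, but usual care may start melatonin as a treatment while EA and SEA may not, so the EA versus usual care contrast can reflect administered hormone

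*Protocol article*

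**What the plan says.** **Purpose.** Under Secondary outcomes, "the levels of salivary melatonin and cortisol will be assessed". Table 2 places the sample at visit 1 and visit 11 (weeks 1 and 5) in all groups. The Discussion gives the aim: "the levels of melatonin and cortisol will be analysed before and after treatment to explore the physiological mechanism of EA in the treatment of insomnia". It supports this partly with a report that acupuncture raised the body's own nocturnal melatonin secretion. The same paragraph recognises melatonin as a therapy: "several previous studies reported the efficacy and safety of using melatonin to treat insomnia".

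**Permitted co-treatment.** Interventions treats the arms differently. For usual care: "The usual care group will be allowed to undergo any treatment for insomnia except traditional medicine such as acupuncture, moxibustion, and herbal treatment". For the two needling arms: "The EA and SEA groups will be prohibited from undergoing any additional treatments for insomnia during the study period".

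**Entry.** The exclusion criteria remove as-needed insomnia medication in the previous 2 weeks and "a change in the type or dosage of a regularly taken medication in the previous 4 weeks to alleviate insomnia". Unchanged regular medication is therefore admitted, and randomisation is stratified on whether insomnia medication is taken.

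**Analysis.** For the secondary outcomes, including "changes in melatonin and cortisol levels, will be the same as those used for the primary assessment analyses", the method is an analysis of covariance (ANCOVA) on baseline and treatment group by intention to treat, with Dunnett's test between groups. Concomitant treatments are recorded on the case report form (CRF).

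**The concern.** The mechanistic question concerns what the participant's own body secretes. For the ISI, permitted co-treatment is part of the usual-care strategy, and intention to treat compares strategies sensibly. For melatonin, the co-treatment can be the molecule being assayed, so the same analysis does not answer the question set in the Discussion.

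The two contrasts are affected differently.

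- **EA versus usual care.** Melatonin may be started between the two samples in one arm only. A rise in usual care would hide or reverse an EA-related rise. If EA had no effect, it would make EA appear to lower melatonin.
- **EA versus SEA.** The co-treatment rule is the same and medication use is a stratification factor. Regular users add variation, for instance when the interval between dose and sample differs between visits, but no expected difference between arms.

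**Working it through.** **Step 1: the plan's own figure.** The sample size inputs are a difference of 4.15, an SD of 6.0, two-sided alpha 0.025 and 80% power. Then n = 2(2.241 + 0.842)² × 6.0² / 4.15² = 39.7, so 40 per arm, 120 in total, and 120/0.8 = 150. The stated size reproduces by the normal approximation. This point does not affect it; 40 per arm is used below.

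**Step 2: the rules side by side.**

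| | EA | SEA | Usual care |
|---|---|---|---|
| Stable regular insomnia medication at entry | allowed | allowed | allowed |
| New non-traditional insomnia treatment after randomisation | not allowed | not allowed | allowed |
| Melatonin named as excluded | no | no | no |
| Medication term in the stated ANCOVA | none | none | none |

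Stratification balances medication use at entry. It cannot control use begun afterwards.

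**Step 3: bias in EA versus usual care (assumptions).** The article gives no usage rate and no assay SD. Suppose a share p of usual care starts melatonin, nobody in EA does, each user's measured change rises by k SD, and EA has no effect.

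- Bias = p × k. For p = 0.05, k = 2 it is 0.10 SD. For p = 0.20, k = 10 it is 2.0 SD.
- Variance in usual care V = 1 + k²p(1 − p), and SE = √((V + 1)/40).
- At p = 0.05, k = 2: V = 1.19, SE = 0.234, and the false-positive rate is about 4%.
- At p = 0.20, k = 10: V = 17, SE = 0.671, and the rate is about 77%.

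The nominal rate is 2.5%, before any Dunnett adjustment. These are normal approximations to a skewed mixture and are rough. If k is near 0, which an unfavourable interval between dose and sample could produce, there is no bias.

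**Step 4: can one or two users produce significance?** Fix the number of users at m of 40. An extreme value raises the SD along with the mean. With no other effect and k growing without limit, the two-arm t tends to √(39m/(40 − m)):

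- m = 1: √(39/39) = 1.00
- m = 2: √(78/38) = 1.43
- m = 4: √(156/36) = 2.08
- m = 5: √(195/35) = 2.36

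The two-sided 0.025 critical value is about 2.29, so about five users are needed. If the variance is pooled over three arms, t is multiplied by √1.5, giving 1.22 and 1.75 for one and two users against about 2.27. Four users then suffice (2.08 × 1.22 = 2.55).

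**Step 5: precision in EA versus SEA (assumptions).** If a share p of both arms has a drug-driven change of k SD, the expected bias is k(p − p) = 0 and the false-positive rate stays near 2.5%. The SD is multiplied by √(1 + k²p(1 − p)): 1.17 at p = 0.10, k = 2, and 4.12 at p = 0.20, k = 10. Baseline adjustment would remove part of this for stable users.

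**The case against.** **The article is condensed.** Pre-sample restrictions and the handling of users normally sit in the full protocol, a laboratory manual or the analysis plan. The article mentions visit scheduling and training on the saliva kit without giving the content of that training. This stands to the extent that a sampling rule may exist. It does not dispose of the point, because the conflicting elements are all stated: the purpose of the assay, the arm-specific permissions, and the choice to analyse melatonin like the ISI.

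**Safeguards exist.** As-needed medication in the previous 2 weeks excludes; medication use is stratified; EA and SEA may add nothing; baseline is a covariate; the sleep diary covers sleeping aids and the CRF covers concomitant treatment. This stands for EA versus SEA, where no expected bias remains. It does not cover melatonin started in usual care after randomisation.

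**The size is assumed.** This stands in full. No document supports a particular usage rate or elevation, and the elevation depends on a dose-to-sample interval that the article does not give.

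**Stronger readings to avoid.** A reader might infer that a few participants can decide the melatonin result. Step 4 shows otherwise: one or two extreme users can move the point estimate and cost precision, but do not by themselves reach significance. A reader might also extend the point to cortisol and ask that corticosteroid users be left out. The article names no corticosteroid as an insomnia treatment and gives no basis for that.

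**Conclusion.** The concern holds in limited form. As written, the plan lets administered melatonin enter an outcome meant to reflect endogenous secretion, under rules that differ between usual care and the two needling arms. EA versus usual care on melatonin can be biased; EA versus SEA mainly loses precision. Under the stated assumptions the bias runs from 0.1 to 2.0 SD, and the SD in EA versus SEA grows about 1.2-fold to 4.1-fold. Those ranges show sensitivity and are not estimates for this trial: actual use may be low, and the true size cannot be derived from the article. Melatonin is a secondary outcome with an exploratory purpose. The primary ISI analysis and the sample size are untouched.

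**What to change.** In Statistical analysis, separate melatonin from the outcomes analysed like the ISI, and state before unblinding:

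1. The mechanistic reading of melatonin rests on EA versus SEA; usual care is reported descriptively.
2. The all-randomised analysis is kept.
3. Beside it stands an analysis without participants recorded on the CRF as taking melatonin. The main restriction is regular use at visit 1, a baseline characteristic.
4. A further sensitivity analysis also leaves out those using melatonin by week 5. It is labelled as such because that use arises after randomisation and may differ by arm.
5. The number of melatonin users is reported per arm at visit 1 and by week 5.

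The co-treatment rules and the purpose of the assay need to be reconciled in the text; no change to those rules is proposed here. The cost is analysis wording and use of medication records already planned for the CRF. The downside is slightly fewer participants in a supporting analysis of an exploratory outcome. The article reports that recruitment is under way, so the wording can still be set before the data are unblinded.
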